#### Analysis

The data to support the primary ITS analysis will come from the BIS. The MND implementation occurred from November 2012 to March 2013, allowing time for all hospitals to gain experience with data entry and use of the dashboard. MND data for the 3-year pre-implementation period (November 2009–October 2012) and the 2-year post-implementation period (April 2013–March 2015) will be available after April 2016. Thus, each site will contribute 3 years of data to the pre-implementation phase and 2 years after implementation. We will exclude data from the 5–6 months between the pre- and post-implementation phases from the analysis. For our primary ITS analyses, the six KPIs will be expressed as monthly proportions after pooling across all hospitals. Pooling is necessary to allow inclusion of low birth volume hospitals and to accommodate all six KPIs, including two that assess performance of uncommon outcomes. Time series plots will be used to visually inspect the immediate and long-term effect of the intervention and the presence of trends, cyclical patterns, and outliers. A segmented regression analysis will be completed using separate intercepts and slopes for the time periods before and after implementation of the MND [26, 31]. The presence of autocorrelation will be assessed using Durbin-Watson tests, as well as visual inspection of residual plots. If autocorrelation is present, an autocorrelation parameter will be included in the model. The results of the segmented regression analysis of each KPI will be reported as level and trend changes after the intervention, with 95 % confidence intervals (CI). All analyses will be conducted using SAS v. 9.4.

#### Sample size considerations

The ITS analysis will include monthly data aggregated from 94 hospitals over 5 years (60 time points total). Recommendations are to include between 40 and 50 observations for robust statistical analysis of ITS designs [32]; moreover, to avoid over-fitting of segmented regression models, at least 10 observations for each regression coefficient is required [33]. With 4 regression coefficients in our planned analyses, 60 time points is adequate. Furthermore, to help ensure stability of the monthly proportions, it is recommended that measurements be based on at least 100 observations at each time point. After pooling across all hospitals (approximately 12,000 births per month), the minimum monthly denominator will range from approximately 200 (repeat Caesarian section) to 7800 (group B Streptococcus screening). Thus, we expect to have sufficient sample sizes to ensure stable estimates.

### Objective 2—to explore factors that potentially explain differences among hospitals’ use of the MND

#### Methods

##### Hospital selection

A criterion-based approach [34] will be used to identify a purposeful sample of up to 20 hospitals reflecting different levels of care (levels 1, 2, and 3) [35], annual birth volumes (<1000, 1001–2500, >2500), geographic locations, and degree of engagement with the MND (i.e., none, partial, or full). This approach to hospital selection will provide a diverse sample of hospitals from which to recruit participants for the interviews and ensure a rich source of data to inform our understanding of factors potentially associated with differential effectiveness of the MND.

##### Sampling procedures

In qualitative research, there are no standardized rules for sample sizes: while 6–8 participants often suffice for a homogeneous sample, 20–30 may be needed when looking for disconfirming evidence or trying to achieve maximum variation [36, 37]. We will use the concept of data saturation to determine when no additional interviews are required (i.e., no new information is emerging) [38, 39]. Directors or managers of the maternal-newborn units from up to 20 of the purposefully selected hospitals (key informants) will be invited to participate in an interview. Recruitment may be augmented through snowball sampling. We do not anticipate problems recruiting participants because of our extensive connections with these centers. Following ethical approval, we will identify individuals within each organization willing to participate, who can provide information regarding use of the MND with regard to its utility as an A&F tool for practice change. Participants will be recruited based on their familiarity with the BIS, their ability to describe practice from the perspective of the organization, their knowledge of the KPIs in the MND, and quality improvement within their organization. Participant consent will be obtained prior to scheduling the interviews.

##### Semi-structured interview guide

Key informant interviews will be completed using a semi-structured interview guide. Interview questions will be based on the concepts in the PARiHS framework and the Organizational Readiness for Knowledge Translation (OR4KT) Tool [40, 41], a comprehensive evidence-based instrument that was developed based on a systematic review of conceptual models/frameworks of organizational readiness for change in health care. The OR4KT has been validated in primary care settings and contains questions covering six dimensions of organizational readiness (organizational climate for change, organizational contextual factors, change content, leadership, organizational support, and motivation). The interview questions will be designed to probe participants’ perspectives about the attributes of the MND, hospital contextual factors, and facilitation/support issues that have influenced their hospital’s use of the MND. Interviews, which may last up to 1 h, will be conducted in person or by telephone and will be audiotaped, with consent. The interview guide will be pilot tested and questions revised if necessary.

##### Data entry and processing

Interviewing, transcription, and analysis will proceed concurrently to monitor the progress of the interviews, permit follow-up of issues that may emerge from the data, and allow probing of emerging themes in subsequent interviews [42, 43]. Digital recordings will be transcribed verbatim and verified by the interviewer prior to analysis. Data will be imported into NVivo 11™ (qualitative data management software) to facilitate management of data analysis [44].

#### Analysis

##### Within-case analysis

Initially, data from each of the cases (hospitals) will be analyzed independently. Analysis will begin with repeated reading of transcripts and field notes, summarizing key information by writing a description of each transcript [34, 45], followed by qualitative content analysis using coding, categorizing, and thematic description [43, 46, 47]. Codes will be sorted into (1) a priori categories based on PARiHS concepts (MND attributes, OR4KT dimensions [40, 41], and facilitation factors) and (2) categories that emerge during the analysis [34]. The final step in this within-case analysis will be the development of narrative descriptions of themes derived from each case. Member checking will be undertaken involving a small subgroup of participants to ensure that the themes identified through the coding process resonate with the participants’ experiences and to identify any gaps in the analysis or issues requiring further consideration [34, 48]*.*

##### Cross-case analysis

Subsequently, thematic similarities and differences between cases (based on hospital selection criteria) will provide understanding of the key factors influencing the use of the MND in different practice settings. Investigators will regularly discuss the coding template, categories, and emerging themes to build consensus regarding study findings. The findings will be used to generate hypotheses about factors that explain variability in performance after implementation of the MND and to inform development of a survey to measure these factors in all maternal-newborn hospitals in Ontario.

### Objective 3—to measure factors hypothesized to be associated with differential effectiveness of the MND

#### Methods

##### Sampling procedures

For each maternal-newborn hospital in the province, an individual knowledgeable about organizational structure, quality improvement, and clinical practice, such as the obstetrical director, will be invited to complete the survey. Following ethical approval, we will initiate contact with these potential respondents by email and provide information about the purpose of the study, how the survey results might be used, the confidentiality of the data, and an invitation to participate.

##### Questionnaire development

Information obtained from the key informant interviews (objective 2), concepts contained in the PARiHS Framework, and the OR4KT Tool will inform development of the provincial survey. The survey will be developed using REDCap (Research Electronic Data Capture), a secure, web-based application designed to support data capture for research studies, hosted at the Children’s Hospital of Eastern Ontario Research Institute (CHEO RI) [49]. The survey will have four components (demographic information, questions about the attributes of the MND, clinical behaviors related to the KPIs, and facilitation/user support needs, and the OR4KT questions). The OR4KT questions will be used to explore contextual factors potentially influencing effective use of the MND. New questions will be developed to probe participants’ perspectives about the attributes of the MND and clinical behaviors related to the KPIs (e.g., content and clarity of the information displayed in the MND, evidence supporting each KPI and benchmark, audit features and functionality, and user access). In addition, questions probing the concept of facilitation will be developed focusing on the intensity of the facilitation activities undertaken, satisfaction, and internal and external supports. We will pilot test the survey with clinicians and administrators for clarity, length, and flow of questions, and the questionnaire will be revised if necessary. The OR4KT Tool will be used in its entirety as designed.

##### Survey administration

To promote a high response rate, the survey will be designed and administered using Dillman’s Tailored Design Method [50] for electronic mail surveys. If the response rate has not reached 80 % by weeks 10–12 after reminders, a follow-up phone call will occur.

#### Analysis

Descriptive statistics will be used to summarize characteristics and factors measured in the survey. A list of 18–20 factors will be identified for further statistical analysis (objective 4). To assess the representativeness of the survey, differences in the characteristics of hospitals with and without responses will be investigated using chi-squared and two-sample *t* tests (or non-parametric tests where required).

### Objective 4—to identify factors significantly associated with differences in hospital performance before and after implementation of the MND

#### Analysis

We will conduct a multivariable generalized linear mixed-effects regression analysis of the repeated indicators at each hospital to identify those factors that are most predictive of between-hospital differences in effectiveness of the MND. Unlike the pooled analysis for objective 1, this analysis will use individual hospital-level data. The analysis will be limited to hospitals with annual birth volumes >100 to avoid numerical instability due to small denominators. With an anticipated 60 % response rate for the survey, approximately 50 hospitals will be included in the analysis. Appropriate time intervals for these longitudinal analyses will be chosen to avoid instability due to low denominators: we anticipate that 4 KPIs will be analyzed using quarterly intervals (12 pre-implementation and 8 post-implementation time points) and 2 KPIs will be analyzed using annual intervals (3 pre-implementation and 2 post-implementation time points). The generalized linear mixed-effects regression analysis of the repeated proportions at each hospital will use either a log-link function with the denominator specified as an offset term or a logit link function with the outcome specified in binomial form. For quarterly measurements, time will be modeled using a semi-parametric spline function with knots separating the pre- and post-implementation phases. Random intercepts and slopes will be specified for each hospital, and hospital-specific trends will be estimated using empirical Bayes’ best linear unbiased predictors. An advantage of this model is that estimates can be obtained even for smaller hospitals, as these estimates “borrow information” from the rest of the data, resulting in individual means that are shrunken towards the population mean. For annual measurements, time will be analyzed as a categorical variable and random intercepts will be specified for each hospital. To identify factors associated with differences among hospital trends over time, the candidate predictor variables identified in the survey related to the attributes of the MND (e.g., clarity of the KPI definitions, evidence summaries, visual displays, and audit features), contextual factors (e.g., leadership, culture, formal and informal interactions, and resources), and facilitation factors (e.g., training, resources, internal and external supports) will be entered into the model, together with their product interaction terms with time. To reduce the potential number of coefficients (2 intercepts and 2 slopes, 18–20 candidate predictors, 54–60 interaction terms), we will enter each candidate predictor variable plus its interactions with time separately into the model. Only those factors that have significant main or interaction effects will be considered for the full multivariable model. To arrive at a more parsimonious final model, we will use stepwise backward elimination, first removing interaction terms as necessary and then main effects.

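### The quarterly Objective 4 models have no term for extra quarter-to-quarter variation within a hospital and do not say which time coefficients are random, so the factor-by-time tests can be anti-conservative

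*Protocol article*

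**What the plan says.** The Objective 4 Analysis section of the protocol article sets out the longitudinal model in some detail.

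- **Data.** The article states that "we anticipate that 4 KPIs will be analyzed using quarterly intervals", with "12 pre-implementation and 8 post-implementation time points". The other two KPIs are analysed annually. With the expected survey response, "approximately 50 hospitals will be included in the analysis".
- **Outcome model.** It will be "either a log-link function with the denominator specified as an offset term or a logit link function with the outcome specified in binomial form".
- **Time.** For quarterly KPIs, "time will be modeled using a semi-parametric spline function with knots separating the pre- and post-implementation phases".
- **Random part.** "Random intercepts and slopes will be specified for each hospital". The later count of model coefficients lists two intercepts and two slopes, but the text does not say which of these four vary by hospital.
- **Screening.** Each of 18–20 survey factors is entered separately with its time interactions. Factors with a significant main or interaction effect go forward to a multivariable model, which is reduced by backward elimination.

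No dispersion parameter, hospital-by-quarter effect, residual correlation, robust variance or residual check is named for these models. For the pooled monthly series in Objective 1, the Analysis section says "The presence of autocorrelation will be assessed using Durbin-Watson tests", with an autocorrelation parameter added if needed.

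**The concern.** Once the hospital's random effects are given, a binomial model fixes the remaining variance by the rate and the denominator. At a few hundred women per quarter that variance is small. Staff turnover, local initiatives and lapses in recording can move a single hospital's quarterly rate by more than binomial noise, and neighbouring quarters may resemble each other. If neither the random effects nor a residual term can absorb this, it is left out of the standard errors of the factor-by-time coefficients.

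Those coefficients are what Objective 4 is for: they show whether a survey factor goes with a larger level change or slope change after the dashboard. Standard errors that are too small let chance factors through the screen. The findings are meant to support the design of later cluster randomized trials.

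**Working it through.** **1. The plan's own count.** Two intercepts and two slopes make four time coefficients, so each factor has three time interactions. 18 × 3 = 54 and 20 × 3 = 60, which reproduces the article's 54–60 interaction terms.

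**2. Nominal rate.** The article gives no alpha; two-sided 0.05 is assumed. For three independent tests, 1 − 0.95³ = 0.143. About 14% of null factors would pass at least one interaction test, or 20 × 0.143 = 2.9 of 20, with a correct model.

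**3. Denominator.** Objective 1, Sample size considerations, gives 94 hospitals and a largest pooled monthly denominator of about 7,800 (GBS screening). Per hospital-quarter this is 7,800 × 3 / 94 = 249 on average.

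**4. Scale of the noise.** At a 20% rate, the binomial SD of the logit is √(1 / (249 × 0.2 × 0.8)) = √(1 / 39.84) = 0.16. An extra logit SD of 0.1 moves a true rate of 20% between about 18.4% and 21.6% (±1 SD). An SD of 0.2 moves it between about 17.0% and 23.4%.

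**5. Simulation under the null.**
- Design: 50 hospitals, 12 + 8 quarters with a 5-month gap, and binomial counts with mean denominator 249 and skewed volumes.
- Fit: REML on the empirical logit with known binomial variance, a Gaussian approximation to the mixed model.
- Tests: 110 data sets × 20 null hospital-level factors = 2,200 per scenario. The Monte Carlo SE is about 1 point if the tests are treated as independent.
- Assumptions not in the documents: 20% rate, hospital intercept SD 0.5, slope SD 0.1 per year, the extra quarterly SD, and its lag-1 correlation ρ.

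Share of null factors passing at least one of the three interaction tests (nominal about 14%):

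| Extra SD, ρ | 1 intercept + 1 slope random | 1 intercept + 2 phase slopes random | Both intercepts + both slopes random | 1 intercept + 1 slope, plus AR(1) residual term |
|---|---|---|---|---|
| 0 | 13% | 12% | 9% | 12% |
| 0.05, 0.5 | 19% | 16% | 12% | 13% |
| 0.1, 0 | 28% | 21% | 12% | 12% |
| 0.1, 0.5 | 39% | 28% | 13% | 13% |
| 0.2, 0 | 55% | 38% | 14% | 13% |
| 0.2, 0.5 | 68% | 47% | 13% | 13% |
| 0.3, 0 | 73% | 51% | 13% | 13% |
| 0.3, 0.5 | 83% | 61% | 13% | 13% |

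With one random intercept and one random slope at SD 0.2 and ρ 0.5, the level-change and slope-change tests each reject at 43%, and about 13.6 of 20 null factors pass. With two random phase slopes but a fixed level change, the slope-change test stays at 3–7%. The level-change test then rejects at 14–58% for SD 0.1–0.3.

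**6. Sensitivity to rate and denominator.** Separate simulations used one random intercept and one random slope; the level-change test is nominally 5%.
- 15% rate, denominator 249: 4% at SD 0, 13% at 0.1, 30% at 0.2 and 40% at 0.3.
- 90% rate, denominator 249: 12% at SD 0.1 and 19% at 0.2.
- 15% rate, denominator 249, SD 0.05: 4% for level change and 6% for slope change.
- 15% rate, denominator 100, SD 0.1: 7% and 6%.

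**The case against.** **The article condenses a plan that may specify dispersion elsewhere.** Residual covariance is often left to an analysis plan, and the log-link option names no distribution, so a negative binomial model would be compatible with it. This carries weight. But the article does not leave the random part open: it states the outcome form, the time function, the random terms and a significance screen. Followed as written in binomial form, with one random intercept and one random slope, it gives standard errors that are too small whenever there is appreciable extra variation.

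**The random effects may already be sufficient.** If both intercepts and both slopes vary by hospital, the tests keep their size without any residual term, because the factors are measured at hospital level. This stands in full. The article neither states nor excludes that reading; its two intercepts and two slopes appear only in a count of coefficients.

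**The inflation depends on favourable inputs.** This is also right. The quarterly SD is assumed, 249 is the average for the largest KPI, and that KPI has a target above 94%, not a rate of 15–20%. At a 90% rate, at small SDs or with smaller denominators, the effect shrinks towards nominal.

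**Stronger readings that the documents do not support.** A reader might infer that Objective 4 treats a hospital's quarters as plainly independent draws around one line. They are independent only conditional on the hospital effects, the mean is a spline with a break between phases, and binomial form is one of two options. A reader might also infer that Objectives 1 and 4 contradict each other. Objective 1 fits a single pooled series without random effects, so an autocorrelation parameter is its way of handling dependence; Objective 4 uses random effects for repeated measures. Finally, the rates above are not error rates for the final factor list. Passing the screen only admits a factor to the multivariable model and backward elimination, and that step was not simulated.

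**Conclusion.** The point holds in conditional form. The quarterly models have no term for extra variation or residual serial correlation within a hospital, and the article does not say which time coefficients are random. Under two of the three natural readings (one intercept with one slope, or one intercept with two phase slopes and a fixed level change), modest extra-binomial variation makes the screening tests anti-conservative. Under the third, with all four random, it does not.

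With one random intercept and one random slope, 28–39% of null factors pass at an SD of 0.1 and 55–68% at 0.2, instead of about 14%. Serial correlation makes this worse but is not needed for it. These figures rest on 249 women per hospital-quarter, a 20% rate, alpha 0.05 and an SD that the documents do not give. They show how sensitive the tests are and do not predict what the data will show. The change should be made, because the quarterly analyses depend on these tests and the remedy is cheap.

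**What to change.** In the quarterly models:

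1. Add a hospital-by-quarter random effect, or an estimated dispersion term such as a beta-binomial.
2. Allow first-order autocorrelation within hospital where residuals show it, with spacing that respects the excluded implementation months.
3. State which time coefficients are random, including whether the level change is. A quarterly residual term does not stand in for real differences between hospitals in the level change.
4. Base both the one-at-a-time screening and the final factor-by-time tests on that model.

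The cost is one or two extra variance parameters and wider confidence intervals. In the simulation, adding the residual term to the model with one random intercept and one random slope brought each interaction test to 4–6% and the share passing any test to 12–13%.

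### The Objective 4 models for the two annually analysed indicators leave no room for unexplained hospital differences in change, so the tests that select predictors can reject too often

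*Protocol article*

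**What the plan says.** The relevant text is the Analysis section under Objective 4 of the protocol article.

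- **Time scale.** Four indicators are expected to be analysed by quarter, with 12 points before implementation and 8 after. The remaining two are treated differently: "2 KPIs will be analyzed using annual intervals (3 pre-implementation and 2 post-implementation time points". The article does not name them.
- **Random effects, quarterly indicators.** "Random intercepts and slopes will be specified for each hospital, and hospital-specific trends will be estimated using empirical Bayes’ best linear unbiased predictors".
- **Random effects, annual indicators.** "For annual measurements, time will be analyzed as a categorical variable and random intercepts will be specified for each hospital".
- **Tested terms.** The candidate survey factors "will be entered into the model, together with their product interaction terms with time". A factor goes forward to the multivariable model only if its main effect or an interaction is significant; backward elimination follows.
- **Distribution.** Two options are left open: "either a log-link function with the denominator specified as an offset term or a logit link function with the outcome specified in binomial form". No rule assigns one or the other to an indicator.

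The section mentions no cluster-robust variance, overdispersion term or hospital-by-time effect.

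**The concern.** A survey factor takes one value per hospital, so its interaction with time compares the changes of about 50 hospitals. The relevant error is how much hospitals with the same factor value differ in their change. A model whose only hospital effect is an intercept sets that variation to zero and scales the test by birth-level binomial noise alone. Objective 4 exists because such variation is expected: the Background says audit and feedback works in some settings and not others, and the Objective 2 hospital selection distinguishes no, partial and full engagement with the dashboard.

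Significance is also the entry gate for predictors, so an inflated test puts spurious factors on the list. The Discussion says the study's findings will support the design of later cluster randomized trials.

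**Working it through.** **Reproducing the plan's own count.** The section gives 54–60 interaction terms for 18–20 predictors: 18 × 3 = 54 and 20 × 3 = 60. Three terms per predictor fit a segmented quarterly model with two intercepts and two slopes. Five categorical years give 5 − 1 = 4 terms per predictor. The annual interaction was therefore tested on 4 df, and also as a 1-df factor × post contrast.

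**Inputs from the document**
- About 50 hospitals (Objective 4, Analysis).
- 3 pre and 2 post annual points (same section).
- Smallest pooled monthly denominator about 200, for repeat cesarean, and 94 hospitals (Objective 1, Sample size considerations). Mean per hospital-year: 200 × 12 / 94 = 25.5.

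**Assumptions not in the document**
- An annual indicator has the repeat-cesarean denominator. A mean of 100 is an alternative.
- Event rate 13 % or 30 %; intercept SD 0.6 logits; coefficient of variation of hospital denominators 0.8.
- SD of hospital-specific pre-to-post change, τ, from 0 to 0.5 logits. The central 95 % of hospitals' change odds ratios, relative to the average, is exp(±1.96τ): 0.68–1.48 at τ = 0.2, 0.56–1.80 at 0.3 and 0.38–2.66 at 0.5.

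**Method.** Simulation of a null hospital-level factor. A binomial-logit mixed model with categorical year and random intercepts only was fitted by Laplace approximation, with likelihood-ratio tests at nominal 5 %. There were 400 datasets per cell; the Monte Carlo standard error is about 1 to 2.5 points.

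Type I error, 4 df / 1 df:

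| Mean denominator, rate | τ = 0 | τ = 0.2 | τ = 0.3 | τ = 0.5 |
|---|---|---|---|---|
| 25.5, 13 % | 4.2 / 5.5 % | 6.2 / 9.8 % | 7.5 / 9.5 % | 13.0 / 20.8 % |
| 25.5, 30 % | 4.2 / 4.5 % | 7.8 / 9.2 % | 12.2 / 16.0 % | 14.2 / 23.8 % |
| 100, 13 % | 6.2 / 4.8 % | 10.2 / 15.2 % | 18.5 / 26.5 % | 32.5 / 43.8 % |

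**With a random hospital pre/post change added, τ = 0.5:** 5.0 / 5.0 %, 4.2 / 5.2 % and 5.2 / 5.0 % in the same row order. This check fitted intercept and change as uncorrelated, with the post indicator centred.

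**Effect on selection.** For 20 null factors, one annual indicator, τ = 0.5 and denominator 25.5, the expected number of false interaction findings is 20 × 0.130 = 2.6 to 20 × 0.142 = 2.8 on 4 df, and 20 × 0.208 = 4.2 to 20 × 0.238 = 4.8 on 1 df. At the nominal level it is 20 × 0.05 = 1.

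**Quarterly models.** "Random intercepts and slopes will be specified for each hospital" can mean one intercept and one linear slope per hospital, or a pre and post set for each. A single straight line per hospital cannot represent a hospital-specific step or bend at implementation, so under the first meaning that variation is again left out. The size was not simulated here.

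**Log link with offset.** If the distribution is Poisson, the working variance is np instead of np(1 − p), and the SE ratio is 1/√(1 − p). The p values are the benchmark bands in Table 1, not observed rates.
- GBS screening: 1/√0.10 = 3.16 at 90 %; 1/√0.06 = 4.08 at 94 %. A test with true power 80 % keeps Φ[(1.96 + 0.84)√(1 − p) − 1.96], about 14 % and 10 %.
- Other indicators: formula 1.12–1.15, episiotomy 1.07–1.10, repeat cesarean 1.06–1.08, post-dates induction 1.03–1.05, newborn screening 1.01–1.02.

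**The case against.** **Scope.** A reader might infer that all Objective 4 models carry only a random intercept. The text does not support that: it applies to two of six indicators. For the other four, the wording follows a spline with knots separating the two phases, and the section later counts two intercepts and two slopes. The random effects may well follow that structure, so the quarterly text is unclear but not shown to be wrong. This stands.

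**Size.** A reader might also conclude that the annual tests are badly anti-conservative as a matter of fact. The document gives no SD of hospital-specific change, does not name the annual indicators and contains no hospital-year denominator of 100. With no heterogeneity the test is nominal, and at modest heterogeneity and about 25 per hospital-year the inflation is moderate. The 4-df test, which matches categorical time, is less inflated than the 1-df contrast in nearly every heterogeneous setting. This stands as a limit on size. It does not remove the defect, because zero variation is the one value at odds with the aim of Objective 4.

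**Link.** The log link is one of two listed options, the other is sound, and choosing between them could be left to an analysis plan. No Poisson distribution is named, the error is conservative (opposite to the annual problem), and it is material for one indicator. All of this stands; it supports a restriction for GBS screening and nothing broader.

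**Importance.** Objective 4 is a factor-finding analysis; the Objective 1 effect estimate is untouched. That lowers the weight of the point, but the predictor list is still the main output of this objective.

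**Conclusion.** The point holds for the two annual indicators. Their stated model allows no unexplained between-hospital variation in pre-to-post change, so the tests that select predictors are anti-conservative whenever such variation exists. Its form is certain from the text. Its size is conditional: close to nominal with no variation, up to about 24 % at τ = 0.5 with the repeat-cesarean denominator, and higher only if the unnamed annual indicators have larger denominators. The quarterly models need a clarification, because the document does not establish a fault there. The log-link option is a material problem only for GBS screening, only if Poisson-type, and there it would hide true factors.

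**What to change.** 1. **Annual models.** Add a hospital random effect for the post-implementation indicator, correlated with the intercept. If it cannot be fitted, use hospital-clustered robust variance with a small-sample correction. Name the two annual indicators.
2. **Quarterly models.** State that the hospital random effects include change in level and change in slope at implementation, with a simplified covariance as the fallback if the model does not converge.
3. **GBS screening.** Specify the binomial logit option. For the other five indicators the choice of link matters little at benchmark levels.

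The cost is a few lines of model specification and code. Intervals will be wider where hospitals do differ in change, and some models may need a reduced covariance structure.
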